### Endline survey of mothers/caregivers and their babies

Participating mothers/caregivers in both the 9–18 months and 19–36 month postpartum samples are asked to answer an interviewer-administered questionnaire, which captures the mother’s demographic characteristics, healthcare utilization and engagement (including changes in care location), and her experience with antenatal care, HIV testing, delivery, infant feeding, ART and PMTCT prophylaxis for the eligible child. Mothers of 19–36 month old infants who report being HIV-positive will also be asked more detailed information about engagement in HIV care after their pregnancy, their ART regimen, including reasons for any ART interruptions. Living biological mothers 9–36 months postpartum and infants 9–18 months old will be asked to provide dried blood spot samples for HIV testing. Blood spots will be air-dried onto filter papers and stored at room temperature until they are transported biweekly to the National Microbiology Reference Laboratory in Harare. Maternal samples will be tested for HIV-1 antibody using AniLabsytems EIA kit (AniLabsystems Ltd., [name]) with all positive specimens confirmed using Enzygnost Anti-HIV 1/2 Plus ELISA and discrepant results resolved by Western Blot. Among HIV-infected mothers, dried blood spot samples will be tested for HIV viral load using Biomerieux Easy Mag/Easy Q platform (Biomerieux, France).

Infant samples will be tested if the infant was born to an HIV-positive mother or if the infant was born to a mother whose sample is unavailable. Infant samples will be tested for HIV with DNA polymerase chain reaction (Roche Amplicor HIV-1 DNA Test 1.5). Mothers who participate in the study will have the option to pick up their test results from their local clinic, and will receive appropriate pre- and post- test counseling for her and her infant’s HIV test results from nurses at each health facility.

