Secondary outcomes:3)Viral suppression: The proportion of HIV-infected mothers who are virally suppressed 9–18 months postpartum. The denominator (number of HIV-infected mothers) will be assessed as outlined above. The numerator will be assessed based on laboratory viral load test results. Mothers with viral load test results indicating < 1000 copies/ml will be classified as virally suppressed.4)Postpartum engagement in care (among mothers 19–36 months postpartum): The proportion of HIV-infected mothers who were initiated on ART and who continued ART. The denominator (number of HIV-infected mothers who were initiated on ART) will be assessed using: i) laboratory-confirmed HIV test results, or ii) information recorded on maternal health cards, when available, and iii) self-reported ART status. The numerator (number of HIV-infected mothers who were initiated on ART and continued ART after 19–36 months postpartum) will be assessed based on self-reported ART status at the time of the survey. Additionally, we will calculate the average time between delivery and discontinuation of ART among those mothers who did not continue ART.5)Heterogeneity of the impact of Option B+ on HIV-free survival and MTCT by the extent of integration of PMTCT and ART services at health facilities: Impact heterogeneity of Option B+ will be assessed using community-level cross-sectional serosurvey data as well as data on health facility characteristics from the 157 catchment areas selected as PSUs. The extent of integration of PMTCT and ART services at the facility level will be measured using multiple dichotomous variables such as: whether the facility offers both antenatal and labor/delivery services, whether the facility can initiate pregnant women on ART, whether the facility can continue women on ART after a certain number of months after delivery, whether the facility can offer ART services to male partners, and whether the facility can offer ART services to infants and children. Principal component analysis will be employed to estimate the factor loadings of these variables, in order to calculate an overall integration score per facility.6)Incremental cost effectiveness of Option B+: Assessed using effectiveness data (from the community-level cross-sectional serosurveys) along with costing data (from the 157 health facilities surveys). We will estimate the incremental cost-effectiveness ratio (ICER) of option B+ with respect to option A, and the ICER of option B+ with respect to pre-option A guidelines, as the ratio of the difference in costs over the difference in annually-adjusted effectiveness (for each of the two main outcomes: HIV-free infant survival and MTCT).

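### Retention on ART at 19–36 months is scored from self-report alone, while viral load measured in the same mothers has no stated use

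*Protocol article*

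**What the plan says.** All places are in the protocol article.

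- **Retention numerator** (Study measures, outcome 4): continued ART at 19–36 months "will be assessed based on self-reported ART status at the time of the survey". No other source is named.
- **Retention denominator** (same outcome): "The denominator (number of HIV-infected mothers who were initiated on ART) will be assessed using: i) laboratory-confirmed HIV test results", or "information recorded on maternal health cards, when available, and iii) self-reported ART status".
- **Blood sampling** (Endline survey of mothers/caregivers and their babies): "Living biological mothers 9–36 months postpartum and infants 9–18 months old will be asked to provide dried blood spot samples for HIV testing".
- **Viral load** (same section): "Among HIV-infected mothers, dried blood spot samples will be tested for HIV viral load". No postpartum window limits this.
- **Suppression** (Study measures, outcome 3): "The proportion of HIV-infected mothers who are virally suppressed 9–18 months postpartum", with a cut-off of 1000 copies/ml. Its sources are given as follows: "The denominator (number of HIV-infected mothers) will be assessed as outlined above. The numerator will be assessed based on laboratory viral load test results". The definition referred to is that of the primary outcomes. It admits mothers identified by verbal autopsy or by health card when they are dead or unavailable.
- **Questionnaire** (Endline survey section): both postpartum samples answer a general questionnaire that includes ART. A further module goes to mothers of 19–36 month old "infants who report being HIV-positive will also be asked more detailed information about engagement in HIV care".

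**The concern.** Objective 3 is the assessment of retention in ART services. The Discussion presents it as the test of whether mothers stay on ART after breastfeeding, the assumption on which the expected benefit of Option B+ depends. If a mother who has stopped can be scored as continuing because she says so, the test leans toward confirming that assumption. The viral loads that would show how far it leans are measured in the same women, yet no outcome uses them. The limitations do not mention self-reported ART. By contrast, the Facility survey section does plan to corroborate self-reported information with records.

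Two related gaps sit beside this. The article gives no rule for a mother whose blood is HIV-positive but who reports neither HIV nor ART. Outcome 3 takes over a denominator containing mothers who cannot have a survey viral load, while its numerator needs one.

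**Working it through.** **1. The plan's own sample figure.** Inputs from Statistical power: about 1800 pairs, 11.5% HIV prevalence, 2% refusal. Expected HIV-infected mothers = 1800 × 0.98 × 0.115 = 203, against a stated figure of approximately 200. It reproduces, and no stated number is in dispute.

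**2. Sampling error, for scale.** At n = 200 and 80% retention, the simple 95% half-width is 1.96 × √(0.80 × 0.20 / 200) = 5.5 points; at 90% it is 4.2 points. These ignore any design effect. They also use all 200 infected mothers, whereas the retention base is only those initiated on ART.

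**3. Over-reporting alone.** Let r be true retention among mothers who disclose, and f the share of those who stopped but say they are still on ART. Observed retention = r + (1 − r)f. The documents give neither quantity, so the values are assumptions. With r = 80%:

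| f | Observed | Bias (points) |
|---|---|---|
| 10% | 0.80 + 0.20 × 0.10 = 82% | +2 |
| 30% | 0.80 + 0.20 × 0.30 = 86% | +6 |
| 50% | 0.80 + 0.20 × 0.50 = 90% | +10 |

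Over-reporting can only push the estimate upward.

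**4. Non-disclosure alone.** Let u be the share of ART-initiated mothers who do not disclose, and q their true retention. True retention overall = (1 − u)r + uq. If they are left out, observed = r. If they enter the denominator (for instance by health card) and are scored as not on ART, observed = (1 − u)r. With assumed u = 10%, r = 80% and f = 0:

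| q | True overall | Left out: 80% observed | Scored off ART: 72% observed |
|---|---|---|---|
| 40% | 76% | +4 | −4 |
| 80% | 80% | 0 | −8 |
| 95% | 81.5% | −1.5 | −9.5 |

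The sign depends on a counting rule that the article does not state, and on retention among mothers whom self-report cannot describe.

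**5. Outcome 3.** Set side by side, the denominator admits mothers known only from verbal autopsy or a health card, and the numerator requires a viral load. If a share m of the denominator has no result and stays in, and s is suppression among those tested, the reported proportion is s(1 − m). The article gives no m, so no size can be stated.

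**The case against.** The strongest case on the other side has several parts.

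*Mothers who conceal HIV are never asked about ART.* A reader might infer this from the restricted module. The text does not support it, because the general questionnaire covers ART and goes to both samples. Only the more detailed questions are restricted. A concealing mother may well not report ART, but that is a different statement.

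*Retention will be overstated.* A reader might conclude this outright. Step 3 supports an upward push from over-reporting, but step 4 shows that non-disclosure can work in either direction. The denominator wording is ambiguous, and health cards are a named route in. Nor do the documents say that non-disclosers are the likeliest to have dropped out. Some may be undiagnosed and never started, and so rightly outside a retention denominator.

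*The bias exceeds sampling error.* No rate in the documents supports this. Take one assumed scenario of 200 mothers, with 10% not disclosing, half of those off ART, and 90% of the rest reporting ART. Reported retention is 162/180 = 90%, against (162 + 10)/200 = 86% with everyone counted. That 4-point gap is below the half-widths of 4.2 points at 90% and 4.9 points at 85%. Larger gaps appear if viraemia is treated as non-retention, which it is not.

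*Use all laboratory-positive mothers as the base.* This would replace retention among initiators with coverage, a different estimand.

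*Outcome 3 is biased downward.* The article classifies only mothers who have results and states no rule for the rest. The direction is therefore not fixed by the text, and handling of missing results may lie in an analysis plan that is not shown.

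These objections stand against the stronger readings. They leave untouched that self-report is the only numerator source, that the 19–36 month viral loads have no stated use, and that outcome 3's wording mixes a tested numerator with a denominator that includes mothers who cannot be tested.

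**Conclusion.** The point holds in limited form. Retention at 19–36 months rests on self-report with no planned check, although the check is already being measured. Over-reporting would raise the estimate by an unknown amount: +2 to +10 points at an assumed 80% true retention and 10% to 50% misreporting. Non-disclosure at an assumed 10% could shift it by anything from +4 to −9.5 points, according to how these mothers are counted and how well they are retained. No single corrected figure can be given, because the documents report no rate of misreporting or non-disclosure. Outcome 3's denominator needs rewording, with no size attached.

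The consequence is moderate. Both outcomes are secondary, retention is to be analysed mainly descriptively, and the primary outcomes are unaffected. It is still worth correcting, because the Discussion rests a substantive claim on Objective 3.

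**What to change.** 1. Keep retention among mothers initiated on ART as defined. Add viral suppression (below 1000 copies/ml) at 19–36 months postpartum as a named outcome.
2. Cross-tabulate self-reported ART with suppression at 19–36 months, and report the share of self-reported continuers whose viral load is 1000 or more.
3. Report laboratory-positive mothers who do not report HIV or ART as a separate group with their suppression status, so that they are neither silently dropped nor scored as off ART.
4. If a measure over all HIV-infected mothers is wanted, label it coverage and show it beside retention, not in its place.
5. For outcome 3, restrict the denominator to HIV-infected mothers with a valid viral load result, weighted for missing samples.
6. Add reliance on self-reported ART to the limitations.

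The cost is a few lines of analysis text. The samples and assays are already planned. The drawback is that viral load is not a pure measure of ART use: a mother on ART can be unsuppressed, and a few mothers off ART can fall below the cut-off. That is why both measures are shown and neither replaces the other.

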Sampling fractions for EAs within each catchment area were chosen to target selection of roughly 50 mother-infant pairs per catchment area. Sampling fractions used in in the 2014 survey round to select eligible mother-infant pairs in each catchment area were used as a base to select a comparable proportion of EAs from each catchment area for the 2017–18 round. Adjustments were made to sampling fractions to mandate a minimum selection of 7 EAs per clinic catchment area, or all EAs if there were fewer than 7 EAs associated with a clinic catchment area. In each selected EA, village health workers (VHW) are trained by and work in conjunction with survey staff to conduct a full census of all households in the selected EAs. The VHWs and survey teams use area maps to visit all identified structures, and record the number of potentially eligible mothers and infants by visiting households and conducting a short screening survey to ascertain the presence of eligible mother/caregiver-infant pairs. Within the selected EAs, all eligible mothers who have given birth 9–18 months prior, and all infants 9–18 months old are selected for inclusion in the survey. We will also sample 10% of mothers 19–36 months postpartum in order to assess longer term engagement in care following the end of the breastfeeding period.

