To assess heterogeneity of the impact of Option B+ on HIV-free survival and MTCT among infants 9–18 months of age by the extent of integration of PMTCT and ART services at health facilities (Objective 2) we will first describe the variability in service integration, and characteristics of the facilities and catchment populations. We will capitalize on the variation of the integration score and other facility characteristics across the catchment areas to examine whether they affect the effectiveness of Option B+. We will describe differences in HIV-free survival by these facility-level characteristics. We will employ two identification strategies for these analyses. First, we will model 2017–18 outcomes adjusted for 2012 characteristics in each facility using ordinary least squares regression with HIV-free infant survival (or MTCT) as the aggregate continuous outcome. Similarly, we will model 2017–18 outcomes adjusted for 2014 characteristics. Second, we will apply a “difference-in-difference” approach, in which the outcomes will be defined as a) changes in HIV-free survival (or MTCT) between 2017 and 18 and 2012 in each catchment area, as well as b) changes in the same outcomes between 2017 and 18 and 2014.

Analysis for the retention of mothers in ART services after 19–36 months postpartum (Objective 3) will be primarily descriptive due to small sample size (e.g. 10% of eligible mothers 19–36 months postpartum). We will explore possible variations in the proportion of mothers who continued ART after weaning by whether the HIV-infected mother was or not on ART prior to PMTCT, to assess whether asymptomatic mothers were retained in care. We will also examine the average time between weaning and discontinuation of ART among those mothers who did not continue ART.

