### Statistical power

We hypothesized that differences in HIV-free infant survival and MTCT between Option B+ (2017 estimates) and the pre-Option A standard of care (2012 estimates) will be greater than the differences between Option B+ (2017–18 estimates) and Option A (2014 estimates). Therefore, sample size calculations for the community surveys were conducted targeting the comparison between 2014 and 2017–18 estimates, as described below.

Sample size calculations were based on the formula for unadjusted comparison of proportions within matched pairs (where a “pair” is two measurements of the outcome within the same catchment area e.g. MTCT in a given facility in 2014 and in 2017–18) [21]. Findings from the 2012 survey estimate an average ANC prevalence of 12.5% among mothers in our catchment areas, with 9% of HIV exposed 9–18 month old infants being infected and 10% of HIV-exposed infants being deceased or infected with HIV [9]. In 2014 ANC prevalence was 13.6% among mothers in our catchment areas and the proportion of HIV-exposed infants who were deceased or HIV-infected had dropped to 4.8% [22]. In Zimbabwe the national targets for Option B+ are 95% HIV-free infant survival and less than 5% MTCT. Consequently, we calculated the sample size needed to detect a reduction from 2014 outcome proportions to 3.4% HIV infection or death in 2017–18.

Based on our 2012 and 2014 survey experience, we presume the 2017–18 survey will have a survey refusal rate of 2% and a value of 0.25 for the coefficient of variation (k_m_). Using a two sided-test at a 5% level of significance and a desired power of 80%, we would require a harmonic mean greater than 4 HIV-exposed infants (i.e., infants whose mothers are HIV-infected) per catchment area. We expect that the prevailing trend of decreasing ANC prevalence will continue [23] and therefore assume that ANC prevalence will have decreased to 11.5% by 2017–18. Taking into account variability in both catchment area size and underlying HIV prevalence among pregnant women across PSUs (again, based on our 2012 and 2014 data) we estimate that we will need a sample 13,000 pairs in 2017–18. Using the above assumptions we would have 80% power to detect a difference in HIV-free infant survival between Option A and Option B+.

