For mothers at 19–36 months post partum, under the assumption of a 11.5% HIV prevalence among mothers in 2017–18, and taking into account variation in prevalence and refusal rates similar to those observed in the 2012 and 2014 surveys, we estimated that, in order to measure the proportion of mothers who continued ART after weaning, we would require a sample of approximately 1800 mother-infant pairs, of which approximately 200 mothers are expected to be HIV-infected.

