Finally, the population-level benefits of Option B+ are predicated on mothers being retained in care for life, and our design will be one of the first population-based assessment of retention in HIV care up to 3 years postpartum among mothers who received Option B+. By simplifying service delivery and reducing the number of steps that mothers need to negotiate, Option B+ is expected to improve retention in care and adherence to ART. Given that the postulated benefits of Option B+ are predicated on HIV-infected mothers staying on ART beyond breastfeeding, our study design will test this assumption.

Our study is subject to limitations. Although our estimates account for transmissions occurring during the first 9–18 months of breastfeeding, HIV-exposed infants may still be breastfeeding at the time of the survey (median duration of breastfeeding is 17.8 months in Zimbabwe) [33]. Estimates of HIV-free survival for 9–18 month old infants may therefore overestimate HIV-free survival at 24 months (at the end of breastfeeding) and may result in an underestimation of MTCT. Nonetheless, estimates restricted to all HIV-exposed infants no longer breastfeeding at the time of our 2012 survey were comparable: 91.9% (95% CI: 86.8–95.1) HIV-free infant survival and 8.1% (95% CI: 4.9–13.2) MTCT [9].

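### Time to ART discontinuation is planned as a mean over mothers who have already stopped, from two different origins; this supplementary summary is truncated by the interview window and says little about retention

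*Protocol article*

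**What the plan says.** Under Study measures, secondary outcome 4 is the proportion of HIV-infected mothers who started ART and are still on it at 19–36 months postpartum. Continuation "will be assessed based on self-reported ART status at the time of the survey". The same item then adds a timing summary: "we will calculate the average time between delivery and discontinuation of ART among those mothers who did not continue ART".

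Under Analyses, the paragraph on Objective 3 says the work "will be primarily descriptive due to small sample size" and ends with a different interval for the same group: "We will also examine the average time between weaning and discontinuation of ART among those mothers who did not continue ART".

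The sample is described under Sampling strategy: "We will also sample 10% of mothers 19–36 months postpartum in order to assess longer term engagement in care". Each mother is seen once. Statistical power expects about 1800 pairs, of whom about 200 mothers are HIV-infected.

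Neither sentence on average time mentions mothers still on ART. The article does not say which origin defines the measure, or what happens when a mother has not weaned or stopped ART before weaning.

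**The concern.** A mother interviewed at 19 months can contribute only stopping times below 19 months, and one interviewed at 36 months only times below 36. A mother still on ART contributes nothing. The mean over stoppers is therefore taken from a right-truncated sample. It is governed mainly by the interview window and by whether stopping comes early or late, and hardly by how many mothers stop.

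The Discussion presents the study as a test of whether mothers stay on ART beyond breastfeeding. A reader who sees a mean of about 13 months may take it as a typical duration on ART, or compare it with another programme's figure. It supports neither use.

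Counting from weaning adds a second problem. The interval does not exist for a mother who has not weaned and is negative for one who stopped ART first. Averaging negative and positive intervals, or silently dropping the negative ones, gives quite different numbers.

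**Working it through.** **Inputs from the article.** Interview 19–36 months after delivery (Sampling strategy); about 1800 pairs and about 200 HIV-infected mothers, "under the assumption of a 11.5% HIV prevalence among mothers in 2017–18", and 2% refusal (Statistical power); median breastfeeding 17.8 months (Discussion).

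**Assumptions, not in the article.** Interview time C is uniform on 19–36 months. Time T from delivery to stopping is exponential, with Weibull shapes as sensitivity. The stopping rate is indexed by the true share stopped by 24 months. For the weaning origin, every mother weans at 17.8 months.

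**The plan's own figure.** 1800 × 0.115 × 0.98 = 202.9, which agrees with about 200.

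**Delivery origin, constant hazard λ.** The planned mean estimates

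E[T | T < C] = 1/λ − E[C·exp(−λC)] / E[1 − exp(−λC)].

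Worked case, 50% stopped by 24 months: λ = ln 2 / 24 = 0.0289, so 1/λ = 34.62. The share stopped at interview is E[1 − exp(−λC)] = 0.5435, and E[C·exp(−λC)] = 12.24. The mean is 34.62 − 12.24/0.5435 = 12.1 months.

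Limit at a very low hazard: E[C²]/(2E[C]), with E[C] = 27.5 and E[C²] = (36³ − 19³)/(3 × 17) = 780.3. This gives 780.3/55 = 14.2 months, set entirely by the window.

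| Stopped by 24 months (assumed) | Stopped at interview | Mean among stoppers (months) | True median time to stopping (months) |
|---|---|---|---|
| 1% | 1.1% | 14.2 | 1655 |
| 5% | 5.7% | 14.0 | 324 |
| 10% | 11.4% | 13.9 | 158 |
| 30% | 33.4% | 13.1 | 47 |
| 50% | 54.4% | 12.1 | 24 |
| 80% | 83.3% | 9.7 | 10 |
| 95% | 96.1% | 7.0 | 5.6 |

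**Shape of the hazard.** Mean among stoppers as 24-month discontinuation rises from 5% to 50%:

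| Weibull shape | 5% stopped | 50% stopped | Change (months) |
|---|---|---|---|
| 0.5 (early stopping) | 9.2 | 7.6 | 1.6 |
| 0.7 | 11.4 | 9.7 | 1.8 |
| 1 (constant) | 14.0 | 12.1 | 1.9 |
| 1.5 | 17.1 | 15.0 | 2.1 |
| 2 (late stopping) | 19.3 | 17.0 | 2.3 |

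Within any one shape, a tenfold change in discontinuation moves the mean by about 2 months. Across shapes the order can turn round: 5% stopping, mostly early (shape 0.5), gives 9.2 months, while 50% stopping later (shape 1.5) gives 15.0.

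**Weaning origin, constant hazard.** All interviews fall after 17.8 months, so the share of stoppers with a negative interval is P(T < 17.8) divided by the share stopped at interview. At 50% this is (1 − exp(−0.0289 × 17.8))/0.5435 = 0.402/0.5435 = 74%; at 5% it is 65%. The mean over all stoppers is 14.0 − 17.8 = −3.8 months at 5% and 12.1 − 17.8 = −5.7 months at 50%. Restricted to stops after weaning, it is 6.0 and 5.6 months.

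**The case against.** The strongest reply is that the average is a supplement, meant to say when stoppers stopped. How many stopped is answered by the main proportion, which keeps continuing mothers in its denominator. The shape results support part of this: the mean does separate early from late stopping. The second origin is introduced as a further quantity, so the two sentences can be read as two summaries and not as a contradiction. All of this limits the weight of the point. It does not rescue the number: even as a description of timing, the mean covers only stops that happened before the interview, and neither sentence says so.

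Four stronger readings are tempting and are not supported.

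- A reader might infer that the mean is 12–14 months whatever the drop-out rate. It is not: it is 9.7 at 80% and 7.0 at 95%, and other hazard shapes move it well outside that range.
- A reader might infer that the retention outcome is compromised. The proportion is not affected by truncation of the mean.
- A reader might infer that the comparison by ART before PMTCT would be distorted. Analyses plans that comparison on the proportion who continued, not on the average time.
- A reader might cite the Discussion's remark that "infants may still be breastfeeding at the time of the survey" as evidence about this sample. It concerns the infants aged 9–18 months. The better support is in the Background, which says follow-up is long enough for only some Option B+ mothers to have weaned.

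**Conclusion.** The point holds as a minor one on a supplementary descriptive summary. Both planned means leave out every mother still on ART and are truncated by the 19–36 month window. Under a constant hazard and evenly spread interviews, the delivery-based mean stays at about 12–14 months while 24-month discontinuation runs from about 1% to 50%. The weaning-based mean has no value for some mothers and, with weaning at 17.8 months, is negative for about 65–74% of stoppers when 5–50% discontinue by 24 months.

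The article gives no stopping rate, hazard shape or distribution of interview times, and 17.8 months is a national median applied here to every mother. The exact months therefore illustrate the problem and do not predict the result. The exclusion of continuing mothers and the unresolved origin do not depend on these assumptions.

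**What to change.** Replace both means with one survey-weighted Kaplan-Meier or life-table estimate of cumulative ART discontinuation from delivery. Include all mothers who initiated ART (entering at initiation if that came after delivery) and censor mothers still on ART at interview. Report it at a few fixed times, such as 6, 12 and 18 months. As no interview takes place before 19 months, censoring does not affect these three times.

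Report post-weaning retention separately, among mothers who had weaned and were still on ART at weaning. This answers the weaning question without negative or undefined intervals.

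The analysis remains descriptive. The cost is small but not nil. Stopping and weaning dates are already needed for the planned averages, but ART start dates are also needed for mothers who initiated after delivery, and recalled dates must be good enough to serve as times. Precision is limited: with 200 mothers and no design effect, the 95% half-width is 1.96 × √(0.1 × 0.9/200) = 4.2 percentage points at 10% and 6.9 at 50%. The planned averages are no better placed: if 10–20% of 200 had stopped, they would rest on 20–40 women.
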